##### Sample Size and Power

Based on current release data, we expect to enroll approximately 100 participants over the 18-month recruitment period. At least 100 non-participating formerly incarcerated women with SUD released from prison over the same time period comprise our comparison group, which is built from Oregon state administrative data. Using Markov chain Monte Carlo simulation, the minimal detectable difference between ROAR and non-ROAR groups with 80% power, 5% type I error, and equivalent sample of *n* = 100 in each of the ROAR and non-ROAR groups was computed. It was assumed that varying baseline rates of post-release overdose ranging from 20% and 25% per year, based on data from Oregon Health Authority and the increased risk of overdose in similar populations as reported in the literature. Note that this power analysis has taken into consideration the correlation due to clustering within county level. There are a few scenarios of common correlation for clustering in practice that have been considered while performing the power analysis. Raw risk difference is defined as a raw difference (e.g., p1-p2), and relative risk difference is defined as (p1-p2)/p1.

In the Table 4, we summarize minimum detectable absolute differences with associated relative risks, accounting for varying assumptions about within-county clustering (i.e., correlation).

**Table 4 Tab4:** ROAR power analysis

Minimal detectable differences of post-release opioid overdose as absolute difference and relative risk				
	Baseline rate 20%		Baseline rate 25%	
ρ	Raw risk difference	Relative risk difference	Raw risk difference	Relative risk difference
0.0000	0.105	0.48	0.12	0.52
0.0050	0.115	0.43	0.125	0.50
0.0075	0.120	0.40	0.13	0.48
0.0100	0.120	0.40	0.135	0.46

Calculations assume equivalent sample size of 100 participants for each control and intervention groups, a minimum of 80% power, and alpha level of 5%

Programs that facilitate MOUD in correctional facilities have been previously shown to have a large effect on overdose mortality (RR = 0.4). Given the assumptions described, our pilot is sufficiently powered to detect treatment effects similar to what has been observed in other studies of MOUD delivery through the correctional system (Green et al., 2018).

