**Fig. 1 Fig1:**
[figure not shown]
Conceptual model for ROAR pilot evaluation

Aim 1 collects participant survey data, completes qualitative interview data, and abstracts medical charts to assess: 1) Implementation Outcomes, 2) Service Outcomes, and 3) Client Outcomes. Implementation outcomes examine acceptability, adoption, engagement and retention in the ROAR pilot. Aim 2 evaluates the effects of the ROAR program on our primary outcome of any opioid overdose. This is a binary outcome indicating a fatal or non-fatal opioid-related overdose event in the 6 months following release from incarceration.

#### Aim 1

Pilot the ROAR intervention to reduce risk of overdose among adult women released from prison. ROAR is offered to all eligible female inmates being released to one of Oregon’s four most populated counties over the 18-month recruitment period. The pilot (*n* = 100) includes a process evaluation using quantitative and qualitative measures grounded in the Consolidated Framework for Implementation Research (Keith, Crosson, O'Malley, Cromp, & Taylor, 2017). Baseline participant surveys assess history of overdose, lifetime mental health status and current depression using the Patient Health Questionnaire-9 (PHQ-9). Three-month and 6-month followup surveys of participants assess self-reported return to opioid use, non-fatal opioid overdose and engagement with SUD treatment and recovery support services. Qualitative interviews with participants, CRMs, and clinicians assess barriers and facilitators to retention in treatment and acceptability of the intervention.

#### Aim 2

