### Data collection and measures

Our primary outcome is any opioid overdose (fatal or non-fatal) within 6 months following release from incarceration. This is a binary outcome indicating a fatal or non-fatal opioid-related overdose event in the 6 months following release from incarceration. We identify fatal opioid overdose with linked vital statistics data and define fatal overdose using International Classification of Disease, 10th Revision specific codes for opioid poisoning. Non-fatal overdose is measured using Oregon Medicaid and hospitalization discharge data. We use the date of admission as the overdose date. Emergency department encounters occurring within 1 day of a hospitalization are not counted as distinct overdose events. As secondary analyses, we will examine which baseline characteristics are associated with implementation and client outcomes using both descriptive statistics as well as bivariate methods.

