#### Analysis

##### Opioid Overdose

The primary outcome, opioid-related overdose, is measured using administrative (Medicaid claims, hospital discharge data) and vital statistics. We use hospital discharge data to supplement Medicaid claims data in the event that participants lose or change Medicaid enrollment. The validity of administrative data to identify opioid-related overdose is high (sensitivity = 97%, specificity = 85%) (Green et al., 2019). We use Oregon vital statistics (death certificate data) to ascertain opioid-related fatalities. Oregon has a centralized medical examiner model which is known to provide more consistent and specific reporting of drugs implicated in fatalities (Buchanich, Balmert, Williams, & Burke, 2018; Warner, Paulozzi, Nolte, Davis, & Nelson, 2013).

Our primary analysis will examine the effect of pilot participation on the rate of fatal and non-fatal overdose events. We will calculate person-years of follow-up using the time between release date and subsequent death or study conclusion. Thus, women will contribute to calculations of person-years once they are released, except during subsequent incarcerations or after fatality. We will censor follow-up at the end of Quarter 10 or the date of incarceration if they were in prison as of this date. Our primary outcome (any opioid overdose) will be modeled as a rate with person-years as an offset variable.

We will employ either a mixed logistic model if the outcome turns out a non-rare event, or a mixed poisson model (with poisson approximation to binomial distribution) if the outcome turns out to be a rare event. The effect of ROAR participation will be examined by testing the slope coefficient (i.e., b1, see below) of the main treatment effect variable (ROAR participation yes/no) in the model. We will also adjust the treatment effect using covariates such as age, race/ethnicity, incarceration time, and mental health level of treatment need while incarcerated. We control for correlation due to clustering at county level by including a random effect (i.e., α, see below) in the model.

*Alternatively, the model described below is employed for our analysis:*

g[E(y|x)] = b0 + b1*ROAR,+b2*x + α, where g(.) is a link function (e.g., logit or log link), and b2 is a slope coefficient vector of adjusting covariates included in the model; α is the random effect account for county specificity.

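### The power calculation uses annual overdose rates for a primary outcome defined over 6 months, and the article does not settle which follow-up window governs

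*Protocol article*

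**What the plan says.** Two places in the protocol article define the primary outcome over 6 months. Study design, after Fig. 1, says: "This is a binary outcome indicating a fatal or non-fatal opioid-related overdose event in the 6 months following release from incarceration". Data collection and measures says: "Our primary outcome is any opioid overdose (fatal or non-fatal) within 6 months following release from incarceration".

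The Opioid Overdose analysis section describes something else: "Our primary outcome (any opioid overdose) will be modeled as a rate with person-years as an offset variable". Person-time runs from release to death or study conclusion, excluding reincarceration, and "We will censor follow-up at the end of Quarter 10 or the date of incarceration if they were in prison as of this date".

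Sample Size and Power assumes "varying baseline rates of post-release overdose ranging from 20% and 25% per year" and computes minimal detectable differences "with 80% power, 5% type I error, and equivalent sample of" 100 per group. It defines these as differences p1-p2 and tabulates them in Table 4. It then notes that correctional programmes for medication treatment "have been previously shown to have a large effect on overdose mortality (RR = 0.4"), and concludes that the pilot has sufficient power for effects of that kind.

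**The concern.** A risk stated per year is entered as the comparison-group proportion for an outcome that closes at 6 months. Unless all the first-year risk falls in the first half-year, the comparison group will have fewer events than Table 4 assumes, and power will be lower than claimed. At a 6-month control risk of 10.6%, the smallest tabulated difference (0.105) would leave almost no overdoses in the ROAR group.

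The benchmark effect is also quoted for fatal overdose, whereas the outcome counts fatal and non-fatal events together.

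Aim 2 is one of the study's two primary aims. A reader who accepts the adequacy statement could take a non-significant result as evidence against an effect when the comparison may have had little chance of detecting one.

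**Working it through.** **Inputs from the article.** Baseline 20% and 25% per year; 100 per group; 80% power; alpha 5%; relative risk (RR) 0.4; outcome window 6 months, or person-years to the end of Quarter 10. Sidedness is not stated; two-sided is assumed unless noted.

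**Step 1: the plan's own figures.** Table 4 at rho = 0 gives differences of 0.105 and 0.12.
- 0.20 - 0.105 = 0.095, and 0.095/0.20 = 0.475 (printed 0.48).
- 0.25 - 0.12 = 0.13, and 0.13/0.25 = 0.52 (as printed).

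So the tabulated numbers are consistent with the annual figures standing as p1. (The column holds p2/p1, although the text defines it as (p1-p2)/p1.)

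Pooled-variance power is Φ{[(p1-p2)√n - 1.96√(2p̄(1-p̄))] / √(p1(1-p1)+p2(1-p2))}. For 0.20 vs 0.095 this is Φ[(1.05 - 0.983)/0.496] = 55%. For 0.25 vs 0.13 it is 58%. One-sided, the values are 67.5% and 70%. The table is therefore not reproduced as a two-proportion test even on the annual figures. A Poisson rate comparison gives 80-81% at these entries with about 2.2 person-years per woman two-sided, or about 1.75 one-sided. The article does not say which calculation was simulated.

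**Step 2: the 6-month outcome.** The documents give no 6-month risk. Under a constant hazard (assumption) it is 1-√(1-0.20) = 0.106 and 1-√(1-0.25) = 0.134. With RR 0.4 the ROAR risks are 0.042 and 0.054. The pooled formula gives 40% and 50%. Exact enumeration of the same two-sided test gives 41.0% and 51.4%. About 266 and 205 women per group would be needed for 80%.

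Exact power for RR 0.4 with 100 per group and no clustering, by assumed share of the annual risk falling within 6 months:

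| Share within 6 months | Control risk (20% / 25% baseline) | Power |
|---|---|---|
| Half | 10% / 12.5% | 39% / 48% |
| Constant hazard | 10.6% / 13.4% | 41% / 51% |
| 70% | 14% / 17.5% | 53% / 64% |
| 90% | 18% / 22.5% | 65% / 76% |
| All | 20% / 25% | 70% / 82% |

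**Step 3: what moves these figures.** The comparison group is described as at least 100. As an illustration, 60 releases a month, half outside the pilot counties, over 18 months with a 40% opioid history gives 60 × 0.5 × 18 × 0.4 = 216. This is an assumption, because the comparison group is defined by documented substance use disorder instead. With 216 comparators, power is 48% / 60% under a constant hazard, 62% / 75% at a 70% share and 76% / 87% at 90%. Clustering works the other way: with rho = 0.01 and an assumed 25 women per county, the design effect is 1 + 24 × 0.01 = 1.24, and constant-hazard power with 100 per group falls to about 34% / 42%.

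**Step 4: the person-years analysis.** Let E1 = 100 × rate × T and E2 = 0.4 × E1 be the expected events. Power is Φ[ln(2.5)/√(1/E1+1/E2) - 1.96].
- T = 1: E1 = 20, E2 = 8 gives Φ(2.19 - 1.96) = 59%; E1 = 25, E2 = 10 gives Φ(2.45 - 1.96) = 69%.
- T = 1.75: E1 = 35, E2 = 14 gives Φ(2.90 - 1.96) = 83%; E1 = 43.75, E2 = 17.5 gives Φ(3.24 - 1.96) = 90%.

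The 1.75 is an assumption: uniform release over 18 months, Quarter 10 ending at month 30 from the first release, and no reincarceration, so (30 - 9)/12 = 1.75.

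**The case against.** The strongest reply is that the annual rate is not a mistake. The section describing the primary analysis models a rate with person-time running well past 6 months. For that analysis an annual rate is a valid input, and with about 1.75 person-years per woman RR 0.4 is detectable with more than 80% power. A person-years reading also fits Table 4 better than a two-proportion reading does. This stands as far as it goes: a reader might infer that the annual unit is simply wrong, and the documents do not support that while the two windows coexist. It does not rescue the table, which is labelled as a difference of proportions and states no exposure, although the answer depends on exposure.

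A second reply is that 41% to 51% rests on a constant hazard, whereas the Background describes elevated drug-related death risk in the 4 weeks after release. That also stands. The evidence concerns death and gives no 6-month share for any overdose, so the power has to be shown as a range.

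A third is that the comparison group may exceed 100. This helps, and together with strong front-loading it can bring power near or above 80%. Under a constant hazard even 900 comparators give only 55% and 70%.

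**Conclusion.** The inconsistency is real: the outcome is defined over 6 months, the power inputs are per year, and nothing links them. If the 6-month outcome governs, power for RR 0.4 with 100 per group is about 41-51% under a constant hazard, 53-64% with 70% of the annual risk inside the window and 65-76% with 90%. At that size it reaches 80% only at the 25% baseline with the whole annual risk inside the window. These figures assume a two-sided 5% test and no clustering. If the person-years analysis governs, power is about 59-69% at 1 person-year per woman and 83-90% at 1.75, and the power section omits the quantity that decides between them.

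A reader might infer that the study is shown to have about even odds at best, or that a null result would be close to uninformative. The documents do not support that. It follows only from a constant hazard, a 6-month window and about 100 comparators taken together. What they do support is that the adequacy statement is not established for the outcome as defined, and that its RR 0.4 benchmark refers to a different, fatal-only outcome.

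**What to change.** 1. State one follow-up window for the primary outcome and reconcile Study design, Data collection and measures, and the Opioid Overdose analysis section to it.
2. Give the baseline risk or rate for that window, with its source and the assumed timing of risk after release.
3. Recompute Table 4 on that scale, stating sidedness, person-time per woman if a rate is used, comparison-group size and the clustering assumption.
4. Replace the adequacy statement with the achieved power, or the detectable relative risk, as a range over those assumptions.
5. Label RR 0.4 as an overdose-mortality figure.

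The cost is a recalculation and revised text, with a stated power that is likely to be less favourable. No extra enrolment is needed.

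### Table 4's minimal detectable differences do not reach the stated 80% power with 100 women per group, and its relative risk difference column prints p2/p1 instead of the defined (p1-p2)/p1

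*Protocol article*

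**What the plan says.** The Sample Size and Power section describes a simulation in which the minimal detectable difference for an "equivalent sample of *n* = 100 in each of the ROAR and non-ROAR groups was computed". Table 4's footnote repeats the inputs: "Calculations assume equivalent sample size of 100 participants for each control and intervention groups, a minimum of 80% power, and alpha level of 5"%. The assumed comparison-group values are "baseline rates of post-release overdose ranging from 20% and 25% per year". The raw difference is p1-p2, and "relative risk difference is defined as (p1-p2)/p1". The section adds that "this power analysis has taken into consideration the correlation due to clustering within county level", with correlations from 0 to 0.01. It gives neither the cluster size nor the sidedness of the test.

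The first row of the table is "0.0000 0.105 0.48 0.12 0.52" and the last is "0.0100 0.120 0.40 0.135 0.46". The columns are the correlation, then the raw and relative differences at 20%, then the same at 25%. The section cites a risk ratio of 0.4 for overdose mortality from earlier programmes and concludes that "our pilot is sufficiently powered to detect treatment effects similar to what has been observed in other studies of MOUD delivery".

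**The concern.** With zero correlation, cluster size drops out and the row is an ordinary comparison of two proportions with 100 per group. A drop from 20% to 9.5% looks too small to be detected with 80% power at that size. The relative column also runs the wrong way. Under the definition given, the detectable relative effect at 20% would fall from 0.48 to 0.40 while the raw difference beside it rises from 0.105 to 0.120. Both cannot be true at a fixed baseline.

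Table 4 is the only calculation behind the claim of sufficient power. If it is too favourable, a null result on overdose could be read as evidence against a large effect that the study had a substantial chance of missing. A reader who takes the column as defined would also think a 40% reduction is detectable at the 20% baseline.

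**Working it through.** **Inputs**, all from Sample Size and Power: n = 100 per group; alpha 5%; target power at least 80%; p1 = 0.20 or 0.25; p2 = p1 minus the tabled raw difference. Two-sided testing is my assumption, and one-sided is also shown.

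**Step 1: the plan's own figure, zero correlation.** With d = p1-p2 and p̄ = (p1+p2)/2,

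power = Φ{ [d − 1.96·√(2p̄(1−p̄)/n)] / √([p1(1−p1)+p2(1−p2)]/n) }.

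- 0.20 vs 0.095: p̄ = 0.1475; (0.105 − 1.96 × 0.05015)/0.04960 = 0.135; power 55.4%. Exact enumeration of the same test gives 56.5%.
- 0.25 vs 0.13: p̄ = 0.19; (0.12 − 1.96 × 0.05548)/0.05483 = 0.205; power 58.1%; exact 59.2%.

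The stated 80% is not reproduced. Unpooled variance, arcsine and log-odds versions give 54-59%, and a one-year Poisson rate comparison gives 47-48%. One-sided at 5%, exact power is 68% and 70%.

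**Step 2: what 80% would need, treating the rates as one-year risks.** Solving the formula for d with n = 100, two-sided, gives 0.134 (p2 = 0.066, RR 0.33) at 20% and 0.150 (p2 = 0.100, RR 0.40) at 25%. Solving for n at the printed differences gives 178 and 167 per group.

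**Step 3: rows with clustering.** Ignoring clustering altogether, exact two-sided power is:

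| ρ | 20% baseline | 25% baseline |
|---|---|---|
| 0.005 | 0.20 vs 0.085: 66% | 0.25 vs 0.125: 63% |
| 0.0075 | 0.20 vs 0.08: 71% | 0.25 vs 0.12: 67% |
| 0.01 | 0.20 vs 0.08: 71% | 0.25 vs 0.115: 71% |

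Clustering is included by dividing n by the design effect 1 + (m−1)ρ. Because m is not stated, I took 25 and 50 women per county. At ρ = 0.01 the design effects are 1.24 and 1.49. Two-sided power over the six cells is then about 57-62% for m = 25 and 52-55% for m = 50.

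**Step 4: RR 0.4, the effect relied on** (two-sided, 100 per group).

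| Comparison | ρ = 0 | ρ = 0.01, m = 25 | ρ = 0.01, m = 50 |
|---|---|---|---|
| 0.20 vs 0.08 | about 70% | 60% | 52% |
| 0.25 vs 0.10 | about 80% | 71% | 63% |

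**Step 5: the relative column.**

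| ρ | Baseline | (p1−p2)/p1 | p2/p1 | Printed |
|---|---|---|---|---|
| 0 | 20% | 0.525 | 0.475 | 0.48 |
| 0.005 | 20% | 0.575 | 0.425 | 0.43 |
| 0.0075 | 20% | 0.60 | 0.40 | 0.40 |
| 0.01 | 20% | 0.60 | 0.40 | 0.40 |
| 0 | 25% | 0.48 | 0.52 | 0.52 |
| 0.005 | 25% | 0.50 | 0.50 | 0.50 |
| 0.0075 | 25% | 0.52 | 0.48 | 0.48 |
| 0.01 | 25% | 0.54 | 0.46 | 0.46 |

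All eight printed values are p2/p1. Only the cell where both quantities equal 0.50 also fits the definition. A true 40% reduction at the 20% baseline (0.20 vs 0.12) has about 34% power.

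**The case against.** **The planned model is not a simple comparison of risks.** The baseline values are given per year, and the Opioid Overdose analysis section models a rate with a person-years offset and follow-up censored at the end of Quarter 10. Longer follow-up gives more events. A two-sided Poisson comparison of 0.20 vs 0.095 per year gives 47% power at 1 year, 71% at 1.75 years and 80% at about 2.2 years per woman. Converting the yearly rates to cumulative risks reaches 80% at just under 2 years. This does not rescue the table: the power section states no such follow-up, and Data collection and measures sets the primary outcome at 6 months. If the rates are halved for 6 months, power for the zero-correlation rows is about 29-30%. The objection does show that 0.134 and 0.150 depend on an assumption. A reader might take them as the correct entries, but the article does not give the simulation settings that would establish that.

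**A one-sided test may have been meant.** One-sided, the three differences of 0.120 and 0.135 in the ρ = 0.0075 and 0.01 rows (20%) and the ρ = 0.01 row (25%) do reach about 80%, but only with clustering left out. The section says clustering was included, and the zero-correlation rows still reach only 68% and 70%.

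**The label error is easy to see through.** The caption and the sentence introducing Table 4 speak of relative risks, and the raw differences are printed alongside. The intended quantity can therefore be guessed, and the raw differences are unaffected. The header and the definition are still wrong.

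**One hundred comparators is a floor.** The plan does say at least 100, but the table's footnote fixes 100 and 100.

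**Conclusion.** The point stands. Under the inputs printed with Table 4, the two zero-correlation differences have about 56% and 59% power, not 80%. That result does not depend on cluster size, and one-sided testing does not rescue it. It does rest on reading 20% and 25% as one-year risks; over the 6-month outcome window, power would be lower still. Two-sided, the other rows are also below 80% at any cluster size, with or without clustering. Their exact power cannot be fixed, so only the range of about 52-62% for 25 to 50 women per county can be given. The relative column contradicts its own definition.

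A reader might infer that the pilot is underpowered for RR 0.4 throughout. The documents do not support that: at the 25% baseline without clustering, power is about 80%. The claim of sufficient power fails at the 20% baseline, and at 25% it fails at ρ = 0.01 under the assumed cluster sizes.

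**What to change.** - Recompute Table 4 for 100 per group and print either the detectable differences or the power achieved at the present ones. State the sidedness, cluster size and follow-up period used, and reconcile the per-year rates with the 6-month outcome.
- Relabel the relative column as relative risk (p2/p1), or keep the definition and print (p1−p2)/p1.
- Qualify the sentence on sufficient power: by the one-year-risk calculation, RR 0.4 reaches 80% only at the 25% baseline without clustering.
- Use all eligible comparators in the administrative data, which the wording of at least 100 already allows. Target population gives about 60 releases a month, half to the pilot counties and at least 40% with opioid histories. Applying the 40% to the other half over 18 months gives 60 × 18 × 0.5 × 0.4 = 216. Against 100 participants, power for 0.20 vs 0.08 rises to about 81% at zero correlation, but is only about 70% with a design effect of 1.24. This helps but does not replace the restatement.

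The cost is a rerun of the calculation and a correction to one table and its text, with no extra enrolment. The stated detectable effects will look less favourable.
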